## JHM IRB - eForm A – Protocol

- Use the section headings to write the JHM IRB eForm A, inserting the appropriate material in each. If a section is not applicable, leave heading in and insert N/A.
- When submitting JHM IRB eForm A (new or revised), enter the date submitted to the field at the top of JHM IRB eForm A.

\*\*\*\*\*

### 1. Abstract

Parkinson Disease (PD) is a progressive neurodegenerative disorder that impacts both motor function (including tremor, rigidity, bradykinesia, and gait difficulty/postural instability) and nonmotor function (e.g., cognitive and mood impairments) (Armstrong & Okun, 2020).

Deep brain stimulation (DBS) has been used to manage motor fluctuations or complications of dopamine replacement therapy in patients with PD (Pötter-Nerger & Volkmann, 2013; Quinn et al., 2015). The Medtronic Percept™ PC DBS device is the first commercially available platform for patients with movement disorders that is capable of in vivo brain oscillation recording. This allows for simultaneous delivery of electrical stimulation and recording of the local field potentials.

Rhythmic auditory stimulus (RAS) is a Neurologic Music Therapy (NMT) technique that utilizes an auditory rhythmic cue to entrain gait to a specific rhythm. RAS, as an anticipatory time cue, can be used as both an immediate entrainment stimulus, providing rhythmic cues during movement, and as a facilitating stimulus for planning and executing movements to achieve more functional gait patterns. (M. Thaut & Hoemberg, 2014). The mechanism by which RAS exerts its effects in PD is unclear. It has been suggested that RAS can bypass the impaired frontostriatal gait networks in PD by recruiting cerebellothalamocortical networks; alternatively (or concurrently), RAS may augment the function of those frontostriatal networks (Koshimori & Thaut, 2018) .

Given the separate lines of evidence that RAS and DBS can help improve gait patterns, we propose this study to understand the behavioral and neurophysiological mechanisms of RAS and explore the clinical effects of RAS on DBS in patients with PD. To further explore the potential of music and deepen the understanding of RAS, this study will also be supplemented by a phase involving RAS with melody. The goal is to potentially develop a new tool to reinforce the effect of RAS.

The protocol will consist of two parts (DBS OFF and DBS ON). The order of stimulation states will be randomly assigned to the participants. During DBS ON, participants will receive either their previously optimized stimulation or a calibrated stimulation that mimics their clinically optimized stimulation as closely as possible if the exact stimulation is not possible due to limitations of the Medtronic Device after a 10-minute wash-in/washout period. The researchers will measure participants' gait parameters (cadence, velocity, and stride length) with a 2-minute walk (a set distance of 10 meters during the 2-minute walk) and gait patterns using relevant items from the MDS-UPDRS-III rating scale during stimulation ON (Pre-RAS). The pre-RAS phase will be followed by an RAS intervention phase. The participants will then walk to the metronome beats for eight minutes (4 minutes for the same beat as baseline cadence and 4 minutes for 10% faster than baseline cadence) (RAS), and their gait parameters will be recorded. Within each set tempo, the participants will walk for 2 minutes to a pure metronome beat followed by a 2-minute walk with melody set to the same tempo. To counterbalance the effect of having the melody walk first, the order in which the participants first walk with

melody or without melody will also be randomly assigned. Between each of the 2-minute walks will be a 1-minute break. Finally, immediately after this walking bout, the same assessment as for Pre-RAS will be conducted (Post-RAS). Electrophysiological activity (local field potentials, LFPs) will be collected across all stages (pre, during, and post-RAS) of evaluation.

In DBS OFF, there will be a separate 10-minute washout period if it is taking place after DBS ONs so that the participant's brain circuits can adjust to not being stimulated. Except for the DBS stimulation state, DBS OFF will follow the same protocol as DBS ON above.

## 2. Objectives

This study seeks to investigate the mechanisms of behavioral and neurophysiological rhythmic entrainment using RAS with and without melody for gait patterns in patients with PD who already have the PerceptTM PC DBS device implanted (subthalamic nucleus, STN, and internal globus pallidus, GPi).

### Primary goal:

- A. Comparison of gait parameters (cadence, velocity, and stride length) before, during, and after RAS in DBS ON and DBS OFF state.
- B. Comparison of MDS-UPDRS-III (items 3.9-13) scores in before, during, and after RAS in each DBS ON and OFF state.
- C. Comparison of power spectrum density of Local Fields Potential (LFP) (micro-volts-squared per Hz) in before, during, and after RAS in each DBS ON and OFF state.
- D. Comparison of goals A, B, and C with and without melody.

## 3. Background

### a. Motor Effects of STN-DBS

DBS of the STN (STN-DBS) in Parkinson disease is superior to medical therapy in treating motor symptoms and improving quality of life despite the adverse events associated with DBS (Weaver et al., 2009). However, although STN-DBS has been effective in improving some gait measures reflecting hypokinesia, it has not been uniformly successful in improving certain temporal gait factors and has not always improved gait freezing. Furthermore, given the gradual decline over time in STN-DBS' effectiveness on gait disturbances, a multidisciplinary approach including optimized rehabilitation therapy is warranted (Pötter-Nerger & Volkmann, 2013).

### b. Motor Effects of GPi-DBS

DBS of the GPi (GPi-DBS) has also been shown to improve symptoms and quality of life. While the differences between STN-DBS and GPi-DBS are still being researched, some studies have suggested that STN-DBS allows for greater medication reduction, whereas GPi-DBS may lead to a more direct suppression of dyskinesia without the need to reduce medication (Vitek 2022). Some studies also suggest that GPi leads to a greater suppression of psychiatric symptoms (Liu et al., 2014). Similar to STN-DBS, there has been no recorded uniform success in gait improvement, suggesting a need for a multidisciplinary therapy approach.

### c. RAS

Rhythmic auditory stimulus (RAS) is a Neurologic Music Therapy (NMT) technique that utilizes an auditory rhythmic cue to entrain gait to a specific rhythm. RAS, as an anticipatory time cue, can be used as both a short-term immediate entrainment stimulus, providing rhythmic cues during movement, and as a facilitating stimulus for planning and executing a movement to achieve more functional gait patterns. Cadence, gait velocity, and stride length are the commonly used parameters to monitor changes in a patient's gait. (M. Thaut & Hoemberg, 2014).

RAS has been shown to effectively improve gait velocity, cadence, stride length, and potentially decrease falls in patients with PD (Hausdorff et al., 2007; Pau et al., 2016; M. H. Thaut et al., 2019).

Several mechanisms have been proposed for the therapeutic effects of rhythmic cues in patients with PD. Due to impairments of the basal ganglia and loss of frontostriatal connectivity, patients with PD experience a loss of rhythm perception and timing, resulting in various gait abnormalities in PD, including freezing of gait, decreased stride length and gait velocity, and a rhythmically unstable walking pace (Koshimori & Thaut, 2018). External auditory cueing may activate cerebello-thalamic networks that are generally spared in PD and this may compensate for the PD-associated basal ganglia abnormalities (Koshimori et al., 2019; M. Thaut & Hoemberg, 2014). In addition, it has been hypothesized that the beneficial effects of rhythmic cues may be partly due to modulation of brain activity in the pedunculopontine nucleus (PPN) (Molina et al., 2020). Another possible mechanism for rhythmic cueing in parkinsonism involves rhythmic entrainment: motor synchronization with the auditory system, which remains relatively intact in PD (Matsumoto et al., 2014). Phase-locking values in the beta and gamma frequency bands in PD did not significantly differ from those in healthy persons, indicating that auditory entrainment is still present in PD (Buard et al., 2019). There are some discrepancies in the results, though, as another study that looked at PD patients revealed auditory entrainment in the alpha and beta frequency bands (Te Woerd et al., 2017). To better understand the brain mechanisms behind the positive benefits of rhythmic auditory cueing on motor behaviors in PD, additional research into auditory entrainment is necessary.

d. UPDRS-III Rating & Testing

As a standard protocol to assess the severity of symptoms associated with PD, Movement Disorders Society - Unified Parkinson's Disease Rating Scale (MDS-UPDRS) – III is implemented either during clinic visit or during DBS electrode implantation operation. The purpose MDS-UPDRS-III is to 1) assess the baseline severity of the PD symptoms for subsequent therapeutic intervention 2) to evaluate the clinical efficacy of DBS or other treatments.

Symptoms assessed from MDS- UPDRS-III are categorized across multiple domains in cognitive, mood, behavioral, and motor. The scale ranges from 0 – 4, with a higher scale representing higher severity. Specifically, the motor symptoms of PD, such as bradykinesia, dyskinesia, gait, and tremor, are evaluated using a series of clinical tests.

**4. Study Procedures**

- a. Study design, including the sequence and timing of study procedures (distinguish research procedures from those that are part of routine care).

[figure not shown]

Figure 1. Study Protocol

Participants who complete the consent and enrollment process will either remain for an additional up to 90 minutes following their routine clinic visit at the Johns Hopkins Outpatient Clinic or at a later time point following their routine clinic visit

The protocol will consist of two parts (DBS ON and DBS OFF). The order of stimulation states will be randomly assigned to the participants.

Figure 1 indicates the study protocol. As part of DBS ON, participants will receive their previous clinically optimized stimulation or a stimulation that mimics their clinically optimized stimulation as closely as possible if the exact stimulation is not possible due to limitations of the Medtronic Device. during a 10-minute wash-in period. The researcher will measure participants' gait parameters (cadence, velocity, and stride length) with a 2-minute walk (a set distance of 10 meters during 2-minute walk) and gait patterns using the MDS-UPDRS-III rating scale during stimulation ON or OFF (**Pre-RAS**). The participants will then walk to the metronome beats for four minutes **RAS**) (2 minutes for the same beat as baseline cadence without melody and 2 minutes at baseline cadence 35 with melody), and their gait parameters will be recorded. They will then perform the same task at 10% faster than the baseline cadence and their gait parameters will be recorded. Between each of the 2-minute walks will be a 1-minute break. To counterbalance the effect of having the melody walk first, the order in which the participants first walk with melody or without melody will also be randomly assigned. Finally, the same assessment as the Pre-RAS will be conducted (**Post-RAS**). Electrophysiological activity (e.g., local field potentials, LFPs) will be collected across all stages (pre, during, and post-RAS).

In DBS OFF, there will be another 10-minute washout period so that the participant's brain circuits can adjust to not being stimulated. Except for the stimulation state, DBS OFF will follow the same protocol as DBS ON.

The data captured during triggered events is stored on the device and then can be downloaded in a .json file that can be imported into Matlab for analysis. The data are downloaded from the implantable pulse generator (IPG) to the clinician programmer. This .json file is then downloaded and can be stored on a secure location like OneDrive.

In the course of the assessments and the study protocol, we will record participants' gait and movement patterns. Any recordings will not be used for advertising or non-study related purposes.

We will also obtain participants music reward level using the Barcelona Music Reward Questionnaire

The patients will also be asked to fill out a post-session survey after completion of the study comparing the pure RAS vs melodic RAS interventions.

- b. If your study involves data/biospecimens from participants enrolled under other research studies with a written consent or under a waiver of consent, please list the IRB application numbers for those studies.

No biospecimens from participants in other studies will be used.

- c. Study duration and number of study visits required of research participants.

Number of visits: The study duration will either be held around 90 minutes immediately following each scheduled clinic visit or at a later time point. No additional study visits are required.

Study duration (Figure 1):

- Before the study protocol: Barcelona Music Reward Questionnaire (2 minutes)
- Part 1: up to 4 minutes (including device setup)
  - Washout – 10 minutes
  - MDS-UPDRS III (section 3.9-13) – 2 minutes
  - 2 minute-walk – 2 minutes
  - Break – 1 minute
  - 2minute-walk with metronome beats only at base cadence
  - Break – 1 Minute
  - 2-minute walk with metronome beats and melody at base cadence
  - Break – 1 Minute
  - 2-minute walk with metronome beats only at 110% base cadence
  - Break – 1 Minute
  - 2-minute walk with metronome beats and melody at 110% base cadence
  - Break – 1 minute
  - MDS-UPDRS III (section 3.9-13) – 2 minutes
  - 2 minute-walk – 2 minutes
- Part 2: up to 40 minutes (including device setup)
  - Washout – 10 minutes

- MDS-UPDRS III (section 3.9-13) – 2 minutes
- 2 minute-walk – 2 minutes
- Break – 1 minute
- 2minute-walk with metronome beats only at base cadence
- Break – 1 Minute
- 2-minute walk with metronome beats and melody at base cadence
- Break – 1 Minute
- 2-minute walk with metronome beats only at 110% base cadence
- Break – 1 Minute
- 2-minute walk with metronome beats and melody at 110% base cadence
- Break – 1 minute
- MDS-UPDRS III (section 3.9-13) – 2 minutes
- 2 minute-walk – 2 minutes

d. Blinding, including justification for blinding or not blinding the trial, if applicable.

Participants are blinded to the stimulation state (OFF or ON). Given the significant bias introduced by the patient knowing his/her/their stimulation status during the testing and generally wanting to perform “better” when their DBS system is activated, blinding/masking is required to capture the unbiased effect of RAS and/or stimulation.

e. Justification of why participants will not receive routine care or will have current therapy stopped.

The participants will have their DBS neurostimulators turned OFF and during washout period for approximately 35 minutes (washout period and testing period in DBS OFF state). Participants with DBS not infrequently experience their stimulators being turned OFF during routine clinical programming visits, and in the worst-case scenario, would NOT revert to having more prominent symptoms of Parkinson’s disease that they would experience had they never undergone this elective procedure. Participants with DBS routinely turn their DBS systems off for surgical procedures, MRI’s, and during clinical reprogramming sessions. The study requires this exposure in order to better understand the behavioral and neurophysiological mechanisms of RAS and DBS in improving patients’ gait patterns. Participants will be closely observed by study investigators and DBS specialist throughout the visit and can be reactivated immediately if any uncomfortable symptoms reemerge.

In some cases, the participants will require a DBS ON stimulation group that differs from their clinically optimized stimulation. In order to enable the recording capabilities of the Medtronic device, the sensing leads must be set above and below the stimulating leads. If the participants’ clinically optimized stimulation involves the middle leads, these exact same stimulation(s) can be used in the sensing mode. If not, the participant will receive a calibrated stimulation that mimics the clinically optimized stimulation as closely as possible. The participants will be monitored closely by both their clinician and the study clinician to ensure this difference is tolerated.

f. Justification for inclusion of a placebo or non-treatment group.

Participants will be compared using their with and without RAS in DBS on/off state (within-subject comparison), thus, a placebo or non-treatment group will not be necessary.

g. Definition of treatment failure or participant removal criteria.

Participants will be removed from the study immediately if they experience any untoward symptoms during or after DBS being turned off (in this case DBS will be turned back on at the previously optimized settings).

- h. Description of what happens to participants receiving therapy when study ends or if a participant's participation in the study ends prematurely.

All participants will be instructed to continue their usual medications/stimulation once the study ends.

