## 7. Study Statistics

a. Primary outcome variable.

- Change in gait parameters (cadence, velocity, and stride length) before, during, and after RAS in each DBS ON and OFF state.
- Change in MDS-UPDRS-III (section 3.9-13) scores before, during, and after RAS in each DBS ON and OFF state.
- Change in power spectrum density of Local Fields Potential (LFP) (micro-volts-squared per Hz) before, during, and after RAS in each DBS ON and OFF state.
- Comparison of goals A, B, and C with and without melody.

b. Secondary outcome variables.

N/A

c. Statistical plan including sample size justification and interim data analysis.

- Sample size:

We will attempt to recruit all the patients in the movement disorders clinic who meet the inclusion criteria above. Per our clinic database, we have about 10 potential participants at this time. This pilot data will provide an effect size for a larger study.

- Data analysis:

All outcome measurements are continuous variable (time or scores).

- Independent variables: Stimulation state (ON, OFF), time point (pre-RAS, pure RAS, melodic RAS and post-RAS)
- Dependent variable 1: MDS-UPDRS-III (section 3.9: Arising from chair)
- Dependent variable 2: MDS-UPDRS-III (section 3.10: Gait)
- Dependent variable 3: MDS-UPDRS-III (section 3.11: Freezing of gait)
- Dependent variable 4: MDS-UPDRS-III (section 3.12: Postural stability)
- Dependent variable 5: MDS-UPDRS-III (section 3.13: Posture).
- Dependent variable 6: Cadence (steps/minute)
- Dependent variable 7: Velocity (meter/minute)
- Dependent variable 8: Stride length (meter)

- Dependent variable 9: Power spectrum density of Local Fields Potential (LFP) (micro-volts-squared per Hz)

The Shapiro-wilks test will be used to check the normality of the data.

We will use non-parametric paired-sample tests (e.g., Wilcoxon paired-sample test) as appropriate to compare the mean differences between pre-RAS, pure RAS, melodic RAS and post-RAS in each stimulation state (e.g., DBS ON-pre-RAS vs DBS ON-pure RAS vs DBS ON-melodic RAS, DBS ON-pre-RAS vs DBS ON-post-RAS, and DBS ON-pure RAS vs DBS ON-melodic RAS vs DBS ON-post-RAS; same comparison for DBS OFF state).

Further, the mean differences between DBS ON and OFF over each time period will be compared (e.g., DBS ON-pre-RAS vs DBS OFF-pre-RAS; DBS ON-pure RAS vs DBS OFF- pure RAS; DBS ON-melodic RAS vs DBS OFF- melodic RAS, DBS ON-post-RAS vs DBS OFF-post-RAS).

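### Section 4d masks only the participant, and only to stimulation state; no masking is provided for the rater of the MDS-UPDRS-III primary outcome

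*Protocol*

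**What the plan says.** Protocol section 4d names one masked role and one masked factor: "Participants are blinded to the stimulation state (OFF or ON"). The reason given is that patients who know their stimulation status may try to perform better. The section then concludes that "blinding/masking is required to capture the unbiased effect of RAS and/or stimulation". No other masked role is named there or elsewhere in the protocol.

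Section 7a lists as a primary outcome "Change in MDS-UPDRS-III (section 3.9-13) scores before, during, and after RAS in each DBS ON and OFF state". Section 7c treats items 3.9, 3.10, 3.11, 3.12 and 3.13 as five separate dependent variables. Section 3d describes the scoring: "The scale ranges from 0 – 4, with a higher scale representing higher severity".

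Section 4a has a researcher assess "gait patterns using the MDS-UPDRS-III rating scale during stimulation ON or OFF" at the pre-RAS stage. After the RAS walks, "Finally, the same assessment as the Pre-RAS will be conducted". The order of ON and OFF is randomised; the order of pre and post is necessarily fixed.

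Two further statements bear on the remedy. Section 4a says that gait and movement will be recorded and adds that "Any recordings will not be used for advertising or non-study related purposes". Section 4e says that "Participants will be closely observed by study investigators and DBS specialist throughout the visit".

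**The concern.** An MDS-UPDRS-III item score is an observer's judgement on a coarse scale. Masking the participant removes the participant's expectation but leaves the observer's. That expectation would run in the two directions the study tests: better with stimulation ON, and better after RAS. The protocol's own argument, that knowing the stimulation status biases the result, applies equally to a rater who knows it.

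The study is a pilot intended to supply an effect size for a larger trial. A biased contrast would carry into that planning whether or not it reached significance here. The FDR correction in section 7c controls chance findings among many tests; it does not remove a systematic shift in the scores.

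Who is masked is a design feature that the protocol has fixed, so this is not a detail left to an analysis plan.

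**Working it through.** The protocol gives no figure to reproduce. The sample of about 10 is a count of available patients, with no effect size, standard deviation or power stated. The check sets the sections side by side and counts the contrasts that are exposed.

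**Inputs**
- Masked: participants, to ON/OFF (section 4d).
- Scored by: a researcher, in the session (section 4a).
- Scoring times: once before and once after the RAS walks, in each stimulation state (timetable in section 4c).
- Rater-scored variables: 5 of 9 (section 7c).
- Planned contrasts: time points within each state, and ON against OFF at each time point (section 7c).

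**Contrasts per item, on the 4c timetable**
- Pre against post: 1 in ON + 1 in OFF = 2.
- ON against OFF: 1 at pre + 1 at post = 2.
- Over five items: 5 × 2 = 10 pre/post contrasts and 5 × 2 = 10 ON/OFF contrasts, 20 in all.

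Sections 2 and 7 also speak of scores during RAS, but the timetable places no scoring there. If the items were scored during RAS as well, the count would rise.

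**What protects each set from rater expectation**

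| Contrast | Number | Does the live rater know the condition? | Protection in the protocol |
|---|---|---|---|
| ON vs OFF | 10 | Not stated; the order is randomised, so the state could be hidden | None provided |
| Pre vs post RAS | 10 | Yes, from the fixed sequence | None; participant masking to stimulation is irrelevant here |

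All 20 MDS-UPDRS-III contrasts therefore lack a stated safeguard on the scoring side. Masking the rater to ON/OFF would cover the first 10, imperfectly. Only scoring detached from the session could cover the other 10.

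**The case against.** The strongest reply is that section 4d is about the patient's expectation, gives only that reason, and never claims that rater bias is removed. On this reading its closing words are loose rather than false. That is fair as to motive. The sentence nevertheless claims an unbiased effect of both RAS and stimulation, and participant masking to stimulation cannot deliver that for an observer's score.

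Several stronger readings are tempting and are not supported:
- *The rater knows ON or OFF.* A reader might infer this from the lack of masking, but the protocol is silent. Only knowledge of the RAS phase follows from the text.
- *The means of masking are already in place.* The recordings are not said to be video or to show the scored items. The DBS specialist is said to observe, not to operate the device, and is not said to be a different person from the rater.
- *Rater bias alone would give significance.* One might add the items to a 0–20 sum, suppose a one-point shift in six of ten people with no other change, and obtain an exact two-sided p of 2 × (1/2)^6 = 0.031. No sum is analysed. If the six shifts spread over the five items so that each item has one or two non-zero differences, each p is at least 2 × (1/2)^2 = 0.5. FDR also applies: assuming a family of 20 and a 0.05 level (neither is stated), a lone p of 0.031 faces 0.05/20 = 0.0025. Tests all at p = 0.03125 pass together only if k × 0.05/20 ≥ 0.03125, that is k ≥ 12.5, so at least 13 of 20.
- *Every primary outcome is compromised.* Cadence, velocity, stride length and LFP power are not 0–4 judgements and are less exposed.

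It also stands that masking to ON/OFF may be imperfect, because symptoms can reveal the OFF state.

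**Conclusion.** The point holds in a limited form. Followed as written, the protocol leaves one primary outcome family, five of nine dependent variables, open to rater expectation, while section 4d claims an unbiased effect. For the pre/post contrasts this follows from the fixed sequence. For the ON/OFF contrasts it follows from the absence of any masking provision, not from a statement that the rater is aware of the state.

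The direction of a possible bias is clear, but its size cannot be estimated from the document. The count of 20 contrasts rests on the timetable in section 4c. This is an improvement that should be made, not an error that invalidates the study.

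**What to change.** Amend section 4d so that a team member already present, other than the rater, sets and holds the randomised stimulation state out of the rater's sight, and so that items 3.9 to 3.13 are scored masked to ON/OFF. Section 4e already has investigators, in the plural, and a DBS specialist attending throughout, so this needs wording and a division of tasks but no added staff, visit or participant. The downside is partial unmasking by emerging OFF signs.

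For the RAS phase there are two routes:
- If the recordings prove to be video and an existing team member who was not at the session can score them, items 3.9, 3.10, 3.11 and 3.13 could also be scored from coded, shuffled clips without state or phase labels. With about 10 participants, 2 states and 2 time points, that is about 10 × 2 × 2 = 40 assessments to score. Item 3.12 stays a live score, masked to state only. The live rater should not do this rescoring: in so small a sample that person may remember the session.
- Otherwise, restrict the claim of an unbiased effect in section 4d and report the pre/post MDS-UPDRS-III contrasts as not masked to phase. This costs one sentence in the protocol and one in the report.
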